## Abstract

**Introduction:**

South Africa (SA) has a high HIV prevalence and limited mental healthcare resources. Neuropsychiatric complications such as psychosis onset in people living with HIV (PLWHIV) remains poorly understood. The study aims to compare the socio-demographic, clinical, substance use, cognitive and trauma profile of PLWHIV presenting with first episode psychosis (FEP) to those with the condition but without HIV.

**Methods and analysis:**

This study will compare presentation, course, and outcome of a cohort of PLWHIV and FEP with a control group recruited over a 3-year period. We will prospectively test the hypothesis that the 2 groups are socio-demographically, clinically and cognitively distinct at illness presentation, with higher trauma burden and poorer outcomes in those with the dual burden of HIV and FEP. FEP participants, confirmed by a structured neuropsychiatric interview, will have their socio-demographic, psychosis, mood, motor, trauma and substance use variables assessed. A neuropsychological battery will be completed to assess cognition, while quality of life, psychotic symptoms and HIV markers will be measured at 3, 6 and 12 months.

**Ethics and dissemination:**

The study protocol has been reviewed and ethics approval obtained from the Biomedical Research Ethics Committee (BC 571/18) of the University of KwaZulu-Natal. The results from this investigation will be actively disseminated through peer-reviewed journal publications and conference presentations.

Strengths and limitations of this studyThis study will be among the first to examine the interacting roles of HIV, substance use and trauma in a first episode psychosis (FEP) study in Africa.The study may provide valuable insight into the long-term impact of HIV infection on psychosis presentation which is poorly understood in low-and-middle-income countries.Findings from this study will contribute towards baseline data to guide future studies of patients with FEP.The study is hospitals-based, and this may introduce sample bias and limit generalisability to community samples.Randomised controlled trial design is not possible given that study monitors disease progression.

## Introduction

Psychiatric illness in the presence of HIV and AIDS has been linked to negative health behaviours and poorer clinical outcomes.^1^ The prevalence of HIV among those with serious mental illness (SMI) ranges from 1% to 24%.^2^ Left untreated, mental disorders in people living with HIV (PLWHIV) result in poorer quality of life, greater interpersonal difficulties, increased suicide risk and poor adherence to antiretroviral therapy.

Psychotic disorders are associated with a significant burden of disease, with affected persons often relying on limited public sector mental health resources in low-and-middle-income countries (LMICs).^3^ There is a lack of research on HIV and psychosis in LMICs, particularly sub-Saharan Africa (SSA), despite this region accounting for more than two-thirds of the world’s HIV-positive population.^4^ While research from high-income countries has demonstrated that there is a bi-directional relationship between HIV/AIDS and mental illness, there may be differences in the way this relationship is expressed in SSA.^5^ There is much needed cross-cultural insight into the relationship between HIV/AIDS and psychosis. Culture may influence the patients’ perception and experience of psychosis as well as the clinical presentation. This highlights the need to explore the impact of culture on psychosis.^6^ Studies have also shown variations in the socio-demographic and clinical profile of those with dual burden of HIV and first episode psychosis (FEP) compared with those with psychosis only.^7^

### Socio-demographic profile of PLWHIV and first episode psychosis

There is limited literature on the association of HIV and FEP, with previous studies mainly describing HIV prevalence rates or clinical profiles.^8^ A Ugandan study by Lundberg and colleagues^9^ found that HIV-positive patients with mental illness were more likely to be women and older (40–49 years). A KwaZulu-Natal (KZN) Province, SA, study of patients with FEP reported a higher HIV prevalence in less educated individuals; however, this was a small sample.^8^ In a more recent chart review of patients with psychosis admitted to a psychiatric hospital in SA, HIV-infected patients with psychotic disorders were more likely to be women (74.0%), younger than 50 years (94.0%) and less likely to have secondary education than HIV-negative patients with psychotic disorders (56.0% vs 72.0%).^10^

### PLWHIV and psychosis symptomatology

In a review of the literature, grandiose, persecutory and somatic delusions were the most common psychotic symptoms, followed by hallucinations and mood symptoms in PLWHIV with FEP.^11^ An Italian study found that HIV infection increased the severity of symptoms (more frequently paranoid delusions), was associated with a greater impairment in attention and concentration, and had decreased depressive symptoms.^7^ In addition, PLWHIV and psychosis are more likely to be diagnosed as having a psychosis secondary to another medical condition than a primary psychotic disorder, and have more comorbid medical disorders and increased haematological test abnormalities.^10^ A study in Gauteng province, SA, found that among PLWHIV presenting to psychiatry services, 23 individuals were diagnosed with psychosis due to another medical condition while only two were diagnosed with schizophrenia.^12^ However, there is extremely limited literature on HIV and psychosis symptomatology, particularly from Africa.^8 13^ This suggests a hiatus in the current literature on understanding the nature and severity of psychotic symptoms in PLWHIV, particularly in the African context. There is a need for systematic studies of larger cohorts with standardised tools to better understand how HIV may potentially influence psychosis presentation and course, as well as HIV disease outcomes.

### PLWHIV and FEP and cognition

Cognitive impairment is well established in both psychotic disorders and HIV infection, being exacerbated in psychotic patients with HIV.^13^ Being HIV positive is traditionally associated with a sub-cortical cognitive impairment, the prevalence of cognitive deficits being reported to range from 4% to 99% in a systematic review of HIV research in SSA.^5^

De Ronchi *et al*^7^ described cognitive screen deficits in a sample of 22 patients with FEP living with HIV in Italy. Participants had impaired attention and concentration on the Mini Mental State Examination (MMSE) but no other differences on cognitive impairment. A study of cognitive dysfunction among 156 HIV infected and 322 HIV non-infected patients with psychosis in Uganda assessed them with the MMSE and a neuropsychological battery. They found that PLWHIV and psychosis were more cognitively impaired than HIV-negative psychotic patients at baseline, and although there was some improvement with treatment, they remained more impaired at 6 months, suggesting that HIV worsened cognitive dysfunction in psychosis.^13^ While earlier studies have suggested that psychosis and impairment in cognition were later manifestations of HIV, the Ugandan study demonstrated that both these conditions occur early, as shown by the average CD4 count of 305 cells/µL and the intermediate WHO staging of disease presentation. In addition, impairment in cognition also remained, despite an improvement in the psychotic symptoms.^13^ Further research is warranted to establish the impact of HIV and psychosis on cognition, and whether HIV-related cognitive changes are associated with increased risk for psychosis or modifies psychosis onset or course.

### PLWHIV and FEP and substance use

Studies traditionally suggest an association between substance use in FEP patients and HIV infection.^1^ Substance use patterns vary across the different regions of SA. This may be related to both ethnic and socioeconomic differences.^14^ Davis *et al* confirmed both the growing pattern of substance use as well as the trend of psychiatric comorbidity in KwaZulu-Natal (KZN). The rates of substance use in this province were also significantly higher than that reported in studies of the general population in SA.^14^ Another study of patients with FEP in KZN, SA, reported lower rates of self-reported substance use among HIV-positive than HIV-negative patients with mental illness,^8^ which was further supported by a retrospective chart review of patients with psychosis.^10^ This may suggest that either substance use/misuse may not be a significant factor in HIV transmission in the KZN context, or that the study results were limited by under-reporting or the small sample size. Thus, while the international literature suggests that PLWHIV and mental illness may be vulnerable to substance use, this has not been borne out in the local KZN studies and warrants further research.

### PLWHIV and FEP and trauma

Trauma, particularly early life trauma, is also recognised as an environmental risk factor for psychosis.^15^ A South African study investigated the association between a history of traumatic experiences and the clinical features of FEP. Duration of untreated psychosis, age of and symptoms at onset were assessed in 54 psychotic patients, while 22% were HIV infected. Almost half of the study subjects had witnessed (49%) or directly experienced serious physical assault (45%), both events being associated with positive psychotic symptoms.^16^

The trauma experienced may influence psychosis and HIV outcomes, as found in a systematic review, that hallucinations and delusions were more severe in people with a history of childhood trauma.^17^ In addition, Leserman^18^ reported on the negative association of HIV, stress and depression on the course of HIV in terms of decreasing the CD4 lymphocytes, increasing the viral load and having greater risk for premature mortality.

Exposure to violence and resultant trauma is of major public health concern. In SA, the mortality rate secondary to violence was estimated at 73/100 000.^19 20^ While much research on early trauma has been conducted in developed countries, there is a need to examine the association of trauma and FEP in developing countries.^19–21^

### Course of comorbid HIV and psychosis

PLWHIV and psychosis are more likely to develop comorbid medical disorders, experience side effects of antipsychotic medication, develop metabolic syndrome secondary to ART, have longer length of hospital stay and readmission rates, and have poorer quality of life.^1 10^ However, this has not been tested prospectively in the patients with FEP in the African context with the recent wide availability of ART.

### Aims

The aim of the study is to investigate trends in clinical, substance use, cognitive and trauma presentations in individuals experiencing first episode of psychosis over time, and to compare presentation, course and 12-month outcomes between those with and without HIV.

## Methods

Patients referred to the participating psychiatry units will be screened by the respective treating doctors for eligibility for recruitment into the study. The patients with FEP must fulfil the inclusion criteria and will be referred to the designated investigator at each unit. Once written informed consent has been obtained, the protocol for data capture will be followed, as per the list outlined in figure 1 and table 1, the same protocol being followed for outpatients and inpatients. The clinical examination and psychiatric tests, which take approximately 2 hours, will be undertaken by the investigators who are all medical practitioners. Patient baseline assessments will be undertaken within 6 weeks of treatment during their outpatient visit or following admission to the respective units at baseline. A physical examination, body mass index and waist circumference measure will also be obtained by a medical practitioner. Where possible, collateral information from a next of kin, with the participant’s consent, will also be sought. The follow-up visits will be done at 3, 6 and 12 months as outpatients, and the participants will be reimbursed for travel costs. Attempts will be made to coincide each of these with scheduled clinic follow-up visits and will be performed by the same initial interviewer at each psychiatry outpatient department.

**Figure 1 F1:**
[figure not shown]
List of all study procedures used in the patient assessment.

**Table 1 T1:** Objectives and measures used at each visit in HIV-infected and non-infected participants

Domain	Measures	Source of measures/tool	Visit 1	Visits 2 and 3	Visit 4
			Within first 6 weeks	At 3 and 6 months	At 12 months
Demographic factors	Socio-demographic data	Socio-demographic questionnaire	X		
Mental health outcome (objective 1)	Psychosis	Psychiatric history and MINI	X		
	DUP and pathways to care	WHO Encounter	X		
	Severity and nature of psychosis symptoms	PANSS	X	X	X
	Depression	PHQ9	X	X	X
	Trauma	CTQ	X		
		PCL		X	
	PTSD	Clinician-administered PTSD scale for DSM-V (CAPS 5)		X	
	Motor symptoms	ESRS	X	X	X
	HIV-associated cognitive deficit screen	CAT-Rapid and IHDS	X	X	X
	Social cognition	Neuropsychological battery		X (at 3 months only)	X
	Substance use	WHO ASSIST	X	X	X
	Quality of life	WHO-QOL BREF	X	X	X
	Biochemical haematological and radiological tests	From hospital records: full blood count, liver function test, syphilis and hepatitis test. Cerebrospinal fluid biochemistry and neuroimaging if available			
Clinical markers of HIV (objective 2)	HIV status	Confirmatory HIV ELISA			
	HIV marker	VL if HIV positive	If applicable	If applicable	If applicable
	HIV marker	CD4 if HIV positive	X		

ASSIST, Alcohol, Smoking and Substance Involvement Screening Test; CAPS, Clinician-Administered PTSD Scale; CAT, Cognitive Assessment Tool; CD, cluster of differentiation; CTQ, Childhood Trauma Questionnaire; DUP, Duration of untreated psychosis; ESRS, Extrpyramidal Symptom Rating Scale; IHDS, International HIV Dementia Scale; MINI, Mini International Neuropsychiatric Interview; PANSS, Positive and Negative Syndrome Scale; PCL, Psttraumatic Stress Disorder Checklist; PHQ, Patient Health Questionnaire; PTSD, Posttraumatic Stress Disorder; QOL BREF, Quality of Life; VL, viral load.

The cognitive battery assessment, which takes approximately 2 hours, will be administered by a clinical psychologist, at the 3-month and 12-month visits. Translation services will also be available for patients who require isiZulu translation during the interviews.

Following collating the data for steps 1–13 in figure 1 and table 2,^22–33^ we will perform steps 14 and 15 after voluntary counselling and testing. The required HIV tests, CD4 count and viral load if HIV positive, as per the protocol, will be taken by a medical practitioner at each site. HIV testing will be carried out at baseline for all participants as well as at each visit for HIV-negative participants. A patient with a positive HIV test will be referred to the HIV clinic at the site for further management. Other investigations, such as lipid profile, which are part of routine care, will be captured from the clinical records.

**Table 2 T2:** Cognitive test battery and domains to be tested

Domains	Test
Motor skills	Grip strength^22^, Pegboard^23^
Visuospatial functioning	WAIS-R Block Design, Digit symbol^24^, and Rey-Osterrieth Rey Complex Figure (RCF)—Copy^25^
Verbal memory	Rey Auditory Verbal Learning Test (RAVLT)^26^
Non-verbal memory	RCF—Recall^25^
Problem solving/reasoning	WAIS-R Language test^24^
Language	RAVLT^26^
Word generation	Controlled Word Association Test (COWAT)^27^ Animal Naming (Letter and Category cues)^28^
Attention	WAIS-R Digit Span^24^
Executive functioning	Trail making^29^, RCF^25^, Wisconsin Card Sorting Test (WCST)^30^
Social cognition	Emotion perception (Faces Test)^31^, Theory of mind (Eyes Test)^32^, Social knowledge (Situational Feature Recognition Test) (SFRT)^33^

COWAT, Controlled Word Association Test; RAVLT, Rey Auditory Verbal Learning Test; RCF, Rey-Osterrieth Rey Complex Figure; SFRT, Situational Feature Recognition Test; WAIS, Wechsler Adult Intelligence Scale; WCST, Wisconsin Card Sorting Test.

We are keen to explore impact of pathways of care on socio-demographic and clinical variables. Rehabilitation programmes are limited as many sites lack a multidisciplinary team to support this; however, standard of care includes medication, supportive therapy, psycho-education, referral to psychology if indicated and management of comorbid substance use.

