### Study design and setting

The comparative cohort study will be in keeping with a quantitative, descriptive and longitudinal 12-month design of adult patients presenting with FEP that are either HIV infected or non-infected. The study will take place in the eThekwini District, one of 11 in KZN Province, with an estimated population of 3 442 361 people. The district has a high HIV burden, with an estimated 650 000 people living with the virus in 2018.^34^ In addition, there are only five hospitals in the municipality with psychiatric services managed by a psychiatrist, at which the study will be conducted. The hospitals selected are the four general hospitals with specialist psychiatric services situated in eThekwini: Addington, King Edward VIII, Prince Mshiyeni and RK Khan Hospitals, and at King Dinuzulu Hospital, which serves as the psychiatric hospital for the area. All hospitals have inpatient and outpatient psychiatric services and receive referrals from within the district as well as from urban and rural areas as far south as the Eastern Cape Province and northern KZN.

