### Data management and analysis

All participants will be allocated a participant identification number (PID) code at enrolment, which will be used on samples and documents over the 12-month study period. Data will be downloaded to a secure server and kept in a password-protected system. Laboratory results will be merged into the main dataset using the unique PID.

Data will be entered into SPSS V.24 and the analyses conducted using STATA V.15. The socio-demographic and clinical characteristics of participants will be summarised using means and SD continuous variables. For categorical variables, proportion (%) will be reported. Significant associations in contingency tables (cross tabulations) will be assessed using the standard Pearson’s χ^2^ test. An independent samples t-test will be used for comparing differences in continuous variables between two groups. If there are more than three groups, we will use ANOVA methods. A p value less than 0.05 will be regarded as statistically significant. In addition, we may also apply growth mixture modelling to observe whether subsets of individuals follow distinct trajectories over time.

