### Methodological challenges and study limitations

Several limitations may affect the study, including that it is hospital-based, which may introduce sample bias and limit the generalisability to community samples. Another limitation is the use of tools that have limited validity in the local South African context, as they have not been used previously. Language and cultural barriers in communication will be addressed by an available isiZulu translator. A further limitation of the observational nature of the study is the attendant lack of standardisation of treatment, for which will follow the Essential Drug List (EDL) for hospital level adults (Department of Health, 2015). Although patients will follow the same algorithm, they may be maintained on different medication, depending on the individual patient treatment response. The study will, however, provide an adequate sample representing the clinical profile of patients with FEP and PLWHIV in a resource-constrained setting.

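### The named HIV-group comparisons carry no hospital term, although raters are tied to hospital and rehabilitation resources appear to differ between sites; if HIV mix varies by hospital, clinician-rated and follow-up contrasts are biased

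*Protocol article*

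**What the plan says.** Setting (Protocol article, Study design and setting): "there are only five hospitals in the municipality with psychiatric services managed by a psychiatrist, at which the study will be conducted". Four are general hospitals and one is the psychiatric hospital for the area.

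Raters (Methods, opening paragraph): eligible patients go to a designated investigator at their unit, and follow-up visits "will be performed by the same initial interviewer at each psychiatry outpatient department". Table 1 schedules the PANSS and the ESRS at every visit.

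Background care (Methods, text after Table 2): "Rehabilitation programmes are limited as many sites lack a multidisciplinary team to support this". The same sentence goes on to list a common core: "standard of care includes medication, supportive therapy, psycho-education, referral to psychology if indicated and management of comorbid substance use". The limitations section adds: "Although patients will follow the same algorithm, they may be maintained on different medication, depending on the individual patient treatment response".

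Sampling (Participant selection and sampling strategy): all eligible patients are recruited over three years, with a target of 130 per HIV group. No matching or quota by hospital is described.

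Analysis (Data management and analysis): "An independent samples t-test will be used for comparing differences in continuous variables between two groups". Contingency tables get a Pearson chi-square test, ANOVA is kept for larger numbers of groups, and growth mixture modelling is optional. Hospital does not appear in any of these.

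**The concern.** Hospital can act on the results by two routes. A rater who scores systematically high or low shifts every clinician-rated score at that unit. Because the same interviewer returns at each visit, the shift persists over follow-up. Separately, a site with a multidisciplinary team may offer rehabilitation that another cannot, which could affect course and 12-month outcome.

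Neither route harms the HIV comparison if HIV-positive and HIV-negative participants are spread over the hospitals in the same proportions. The design does nothing to secure that. General and psychiatric hospitals, with referrals from urban and distant rural areas, could well differ in HIV share. If they do, a pooled t-test or chi-square test mixes the hospital difference into the HIV difference. Adjusting for patient characteristics such as sex or education would not in general remove a rater or site-care difference; comparing within hospital does.

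What is at stake is the study's central contrast of presentation, course and 12-month outcome by HIV status, which the article intends to use for management algorithms and policy.

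**Working it through.** **The plan's own figure.** The sample size is not in dispute, but it supplies the group size used below.
- OR 1.857 against a proportion of 0.500 gives p1 = (1.857 × 0.5) / (0.5 + 1.857 × 0.5) = 0.650.
- Two proportions, 0.650 against 0.500, two-sided 5%, 80% power: 170 per group.
- Three repeated measures with correlation 0.5: factor (1 + 2 × 0.5)/3 = 0.667, giving 114 per group.
- Allowing for 10% dropout: 114/0.9 = 127, against 130 stated. The figure reproduces closely and contains no hospital or rater term.
- Completers per group: 130 × 0.9 = 117.

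**Size of the bias.** Group hospitals into two types.
- d = share of the HIV-positive group treated at type A, minus that share in the HIV-negative group.
- b = difference in mean score between hospital types, in SD units, from rating and care together.
- With no true HIV effect, the expected unadjusted difference is d × b.
- Standard error with 117 per group = √(2/117) = 0.131 SD.
- False-positive rate = P(|Z + d·b/0.131| > 1.96), with Z standard normal.

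The documents give neither d nor b, so both are assumed.

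| d | b (SD) | Bias (SD) | False-positive rate |
|---|---|---|---|
| 0 | any | 0 | 5.0% |
| 0.1 | 0.3 | 0.03 | 5.6% |
| 0.2 | 0.3 | 0.06 | 7.4% |
| 0.2 | 0.5 | 0.10 | 11.9% |
| 0.4 | 0.3 | 0.12 | 15.1% |
| 0.4 | 0.5 | 0.20 | 33.4% |

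If b is instead measured against the within-hospital SD, so that the hospital effect also adds to the total variance, the last row falls slightly to 32.0%.

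**What such values of d would mean.** Take two hospital types of equal size.
- HIV shares of 40% and 20%: 0.40/0.60 = 0.667 of HIV-positive patients and 0.60/1.40 = 0.429 of HIV-negative patients are at the first type, so d = 0.238.
- HIV shares of 50% and 15%: 0.50/0.65 = 0.769 and 0.50/1.35 = 0.370, so d = 0.399.

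These shares imply 30% and 32.5% HIV-positive overall, whereas the target is one to one. The illustration therefore also assumes that the HIV-negative participants retained keep the hospital mix of all eligible HIV-negative patients.

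**Which measures are reached.** The rating route applies to clinician-rated scales (PANSS, ESRS, CAPS 5). The care route applies to follow-up course and outcome. Rehabilitation delivered later cannot alter baseline history items such as socio-demographic data, childhood trauma or duration of untreated psychosis. The cognitive battery is given by a clinical psychologist who is not stated to be attached to one site.

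**The case against.** The strongest reply is that site adjustment is usually a matter for the statistical analysis plan, which is not shown, and that the article never says hospital will be ignored. A separate plan may indeed add a hospital term, and its mere absence from a condensed article would not be a finding. The article does, however, name the two-group tests for the comparison, and it gives the site facts that make those tests vulnerable.

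Second, there are real safeguards: one assessment protocol, training at initiation with an annual refresher, a common core of care and a shared treatment algorithm. Keeping one interviewer per patient also protects change over time within that patient. These make a large hospital effect less likely. They do not establish that there is none, and the article describes no check of agreement between raters at different hospitals.

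Third, if HIV status influences which hospital a patient reaches, a within-hospital comparison answers a somewhat different question. The documents do not establish this pathway, and reporting both contrasts meets the point.

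A reader might also infer more than the text supports:
- That the HIV-negative group had different care and raters from the HIV-positive group. Both groups come through the same units and receive the same assessments, and nothing assigns a hospital or rater by HIV status.
- That background care as a whole differs by hospital. The article suggests this only for rehabilitation. Differences in medication are attributed to individual response.
- That every outcome is affected. The two routes reach only the measures listed in the working.

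**Conclusion.** The point holds in conditional form. Raters are tied to hospital, rehabilitation resources appear to differ between hospitals, HIV status is not balanced within hospital, and the named comparisons take no account of hospital. Bias follows if, in addition, HIV mix varies by hospital and hospitals differ in rating or in the effect of care. The documents show neither condition and exclude neither.

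Over the assumed range the consequence runs from nothing (5% false positives) to 0.20 SD and about 33%. The upper end needs both a strongly uneven HIV mix and a half-SD hospital effect, so it is a bound on the illustration and not an estimate. The change is worth making because it is nearly free and uses data already held. The stated sample size is not called into question.

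**What to change.** For clinician-rated scales at all visits, and for follow-up course and 12-month outcomes, make the HIV comparison with hospital as a fixed factor (four indicators for five hospitals). For contingency tables, use a Mantel-Haenszel test stratified by hospital. Report the unadjusted contrast beside the adjusted one, and tabulate HIV status by hospital so that readers can judge the overlap.

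The cost is a sentence or two in the analysis section and four degrees of freedom; hospital is known for every participant. Some precision is lost if the mix is uneven. With two equal-sized hospital types and d = 0.4, the squared correlation between HIV group and hospital type is 0.4² = 0.16. The standard error then rises by a factor of 1/√(1 − 0.16) = 1.09, before any gain from removing between-hospital variation. If the mix is even, the loss is negligible.
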